### Allocation and intervention

Participants allocated to the systemic strategy will receive routine coronary angiography before PTA without a previous non-invasive stress test, and subjects allocated to the selective strategy will undergo non-invasive evaluation of possible myocardial ischemia by using DSE or dTS followed by coronary angiography if the test is obviously positive for ischemia. Clinical decisions are reached by consensus of operators, patients, and family, as usual care in the registration group.

### Angiographic strategy

CAD is defined as significant luminal narrowing (≥50 % diameter stenosis as compared with the size of the adjacent reference vessel) in at least one of the coronary arteries (left main trunk, left anterior descending artery, left circumflex artery, and right coronary artery) or their major branches (diagonal branches, obtuse marginal branches, acute marginal branches, posterior descending artery, and posterior lateral branches). Based on the regulation of Taiwan National Health Insurance, significant CAD needing further revascularization is defined as luminal stenosis of at least 70 % of the major epicardial vessels and bypass graft vessel or their major branches (≥50 % for left main trunk or instent restenotic lesion) with reference vessel larger than 2.5 mm in diameter and moderate area of vulnerable myocardium for ischemia. Intermediate stenotic lesions, luminal stenosis of around 50 to 70 %, should be determined if they are hemodynamically significant by fractional flow reserve. Intermediate lesions with a fractional flow reserve of not more than 0.8 are considered hemodynamically significant and require further revascularization.

### Coronary revascularization strategy

The choice of revascularization procedure, either PCI or coronary artery bypass surgery, depends on the operator’s or cardiovascular team’s suggestion and the patient’s decision. A staged approach (myocardial revascularization followed by PTA) and simultaneous approach (PCI immediately followed by PTA at the same time if clinically suitable) are both allowed. However, PTA followed by myocardial revascularization within 21 days after PTA is also allowed in some participating sites because of local IRB request but should be limited to specific situations, in which the utmost benefit for patients is selected by clinical judgment. The duration from revascularization to PTA should be within 60 days. PCI is performed at the time of coronary angiography by using new-generation drug-eluting (more encouraging) or bare metal stents. Participants were put on dual anti-platelet treatment, including 100 mg aspirin and 75 mg clopidogrel per day, thereafter. Aspirin is used indefinitely, whereas add-on clopidogrel is used for at least 1 month in bare metal stent placement and 3 months in drug-eluting stent deployment. The usual practices of interventionists or surgeons with respect to evaluating the severity of CAD and selecting revascularization strategy are determined through literature review and through a survey of study interventionists or surgeons to achieve consensus. Each study interventionist or surgeon should agree to adhere to the aforementioned intervention protocol. All images of coronary angiography and PCI are recorded. A senior experienced interventionist who is not aware of assignments of study groups will review a sufficient number of the off-line images in an attempt to ensure the adherence of investigators with the protocol. There are no relevant concomitant care and interventions that should be prohibited during the trial.

### Blood sampling and measurement of biomarkers

Blood samples are obtained from peripheral arteries in all study subjects before PTA (20 ml) and after PTA (10 ml) and are prepared and stored for enzyme-linked immunosorbent assay as well as genotyping and measurement of micro-ribonucleic acids in plasma and mononuclear cells.

### Data collection and outcome measurement

The minimum follow-up period is 1 year and the maximum is 3 years. Clinical outcomes are obtained by chart review if the patient is still in the hospital and followed up by clinic visit at 30 days after indexed PTA if the patient has been discharged from the hospital and every 6 months thereafter. If participants miss indicated clinic visits, study assistants will call or directly contact the participants or subjects’ family.

The primary endpoint is the composite major adverse cardiac event (MACE) on long-term follow-up. Pre-specified secondary endpoints include the MACE between the screening and 30 days after PTA, and the composite major coronary event on long-term follow-up. Other endpoints include death from any cause, congestive heart failure requiring hospitalization, and any coronary revascularization. The MACE includes cardiovascular death, non-fatal myocardial infarction, non-fatal stroke, and target vessel revascularization (any unplanned coronary vessel revascularization). The composite major coronary event includes fatal or non-fatal myocardial infarction, recurrent angina pectoris, and target vessel revascularization (any unplanned coronary vessel revascularization). The diagnosis of myocardial infarction and stroke has been previously described in detail [6]. Clinical follow-up will be performed 30 days after PTA and every 6 months until the end of the 1-year follow-up for the last randomly assigned participant. The follow-up schedule is listed in Table 2. All outcome data should still be collected for participants who discontinue or deviate from intervention protocols. The clear definitions of each component of primary and pre-specified secondary endpoints are provided to all assessors, and training of assessors to enhance the quality of measurements is performed on site initiation visit.

**Table 2 Tab2:** Follow-up schedule

	V0	Cath	PCI	CABG	PTA	V1	V2	V3	V4	V5	V6	V7	V8
Time elapse from PTA					0	30 (±7)D	24 (±2)W	48 (±2)W	72 (±2)W	96 (±2)W	120 (±2)W	144 (±2)W	168 (±2)W
CRF	001	002	003	004	005	006	007	008	009	010	011	012	013
Markers/SNPs/miRNAs					X								
CBC	X												
BCS	X												
BW/BH	X												
BP/HR	X					X	X	X	X	X	X	X	X
History and PE	X					X	X	X	X	X	X	X	X

*BCS* biochemistry study, *BH* body height, *BP* blood pressure, *BW* body weight, *CABG* coronary artery bypass grafting, *Cath* coronary catheterization, *CBC* complete blood cell count, *CRF* case report form, *D* days, *HR* heart rate, *miRNAs* micro-ribonucleic acids, *PCI* percutaneous coronary intervention, *PE* physical examination, *PTA* percutaneous transluminal angioplasty, *SNPs* single-nucleotide polymorphisms, *V* visit, *W* weeks

The pre-specified endpoints and serious adverse events (SAEs) should be reported to the data management committee and accompanied with required documents. The primary, secondary, and other endpoints are adjudicated on the basis of pre-specified criteria by an endpoint adjudication committee whose members are not aware of assignments of study groups. A conclusion is determined and achieved by voting or reaching consensus after discussion from members.

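### The early secondary endpoint (MACE from screening to 30 days after PTA) has no fixed length, and its end depends on a post-randomization procedure whose timing can depend on the arm

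*Protocol article*

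**What the plan says.** Under *Data collection and outcome measurement*: "Pre-specified secondary endpoints include the MACE between the screening and 30 days after PTA". No other start or end is given for this endpoint.

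The path to PTA differs by arm (*Allocation and intervention*). The routine arm "will receive routine coronary angiography before PTA without a previous non-invasive stress test". The selective arm is first tested non-invasively, "by using DSE or dTS followed by coronary angiography if the test is obviously positive for ischemia".

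Three sequences of coronary revascularization and PTA are permitted (*Coronary revascularization strategy*). Revascularization may be staged ahead of PTA or done in the same session, with the limit "The duration from revascularization to PTA should be within 60 days". In addition, "PTA followed by myocardial revascularization within 21 days after PTA is also allowed in some participating sites".

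The *Statistical analysis plan* section compares secondary endpoints between the randomized arms as proportions, by intention to treat and per protocol. In Table 2 the visit row is headed "Time elapse from PTA".

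**The concern.** A randomized comparison of proportions needs the same observation period in both arms, starting no earlier than the point at which the arms can diverge and ending at a time the assignment cannot move. This endpoint fails at both ends.

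- **Start.** Screening precedes randomization. Events between the two cannot result from the strategy, so they add noise rather than bias.
- **End.** This is the more serious fault. The window closes 30 days after PTA, and the strategies under test can change the date of PTA. An arm with longer waits is observed for longer and collects more events even if the strategies are equivalent.

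A patient who is randomized, survives and never has PTA has no closing date, yet must be counted under intention to treat. What is at stake is whether a difference in early MACE can be read as an effect of the strategy.

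**Working it through.** **1. The plan's own figure.** None is given for the early endpoint. The only sample size is for the primary endpoint, and it reproduces. Inputs from *Power estimation and sample size calculation*: 40% and 24%, margin 5 points, one-sided alpha 0.05, power 80%, dropout 4%.

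n per arm = (0.40×0.60 + 0.24×0.76) × (1.645 + 0.842)² / (0.16 − 0.05)² = 216. The total is 432, and 432/0.96 = 450. The early window does not enter this calculation.

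**2. Window length from revascularization to close.** Inputs: the 60-day and 21-day limits in *Coronary revascularization strategy* and the 30 days in the endpoint definition.

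- Simultaneous with PTA: 0 + 30 = 30 days.
- Staged before PTA: up to 60 + 30 = 90 days.
- On day 21 after PTA: 30 − 21 = 9 days.

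The time from screening to revascularization comes on top and has no stated limit.

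**3. Effect of window length alone.** Risk in a window of d days is 1 − exp(−h·d), with constant hazard h and no treatment effect. There are two hazards:

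- Higher: h = −ln(0.65)/304 per day. This uses the 35% MACE at a median of 10 months cited in the power section, treated here as the risk at 304 days.
- Lower: h = −ln(0.60)/1095 per day. This assumes that 40% MACE accrues over 3 years.

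| Window | Higher hazard | Lower hazard |
|---|---|---|
| 30 days | 4.16% | 1.39% |
| 44 days (14-day delay) | 6.04% | 2.03% |
| 90 days (60-day delay) | 11.97% | 4.11% |

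If one arm has a share f more patients delayed than the other, the early MACE proportions differ by f × (risk in the longer window − risk in 30 days). For example, at the higher hazard with a 60-day delay and f = 50 percentage points, 0.50 × (11.97 − 4.16) = 3.9 points.

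| Excess share delayed (percentage points) | 10 | 20 | 30 | 50 |
|---|---|---|---|---|
| 60 days, higher hazard | 0.8 | 1.6 | 2.3 | 3.9 |
| 60 days, lower hazard | 0.3 | 0.5 | 0.8 | 1.4 |
| 14 days, higher hazard | 0.2 | 0.4 | 0.6 | 0.9 |
| 14 days, lower hazard | 0.1 | 0.1 | 0.2 | 0.3 |

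Entries are points of early MACE. The document gives neither the delays nor the shares delayed by arm, so both are assumptions.

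**The case against.** The strongest reply is that the effect may be small. Patients are already admitted for elective PTA, PCI is done at the time of angiography, and PCI and PTA may be simultaneous. Sixty days is a ceiling and not an expected wait, and with a 14-day delay every shift above is below 1 point. This stands as a limit on size. It does not give the window a fixed length.

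Three stronger readings are tempting, and the document supports none of them.

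- *The window is biased against the routine arm.* A reader might infer this because more angiography suggests more staged revascularization. But the selective arm has a stress test first, and a positive test can lead to the same staging, which lengthens that arm's window. Revascularization after PTA does not lengthen the window at all. No delay by arm is given, so the direction is open.
- *Harm from coronary procedures before PTA is lost, and the primary endpoint is timed from PTA.* The early window opens at screening and so covers those events. Table 2 has case report forms for catheterization, PCI and CABG ahead of the PTA form. Its PTA-based times schedule visits, and nothing makes PTA the time origin of the primary endpoint. An article may leave that origin to the full analysis plan.
- *A patient who dies before PTA has no window end.* A cardiovascular death before PTA is a MACE inside a window already open, and any death ends observation. The gap concerns survivors without PTA.

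**Conclusion.** The point holds for one pre-specified secondary endpoint. As written, the early MACE window starts before randomization, ends at a time the assigned strategy can influence, and is undefined for survivors who never have PTA. A plain comparison of proportions cannot separate strategy effect from window length.

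The size is uncertain. Against a 30-day risk of about 4.2% (higher hazard) or 1.4% (lower hazard), window length alone could shift early MACE by 0.8 to 3.9 or 0.3 to 1.4 points respectively. Both ranges assume 10 to 50 percentage points more patients in one arm delayed the full 60 days. Shorter delays make it small. The figures rest on a constant hazard and on assumed delays and shares. The primary endpoint and the 432/450 sample size are not shown to be affected. The change is worth making because it is cheap and the present endpoint is not a clean randomized comparison.

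**What to change.** Define the randomized early comparison as MACE within a fixed interval from randomization, the same in both arms, counted by intention to treat whether or not PTA takes place. Ninety days is a reasonable example. The 60-day limit runs between revascularization and PTA, not from randomization, so 90 days will not cover every staged patient. Choose a longer interval if the randomization-to-PTA times, examined pooled over arms, require it. Keep MACE to 30 days after PTA as a descriptive peri-procedural summary without a between-arm test.

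The cost is a change of endpoint wording and one derived date. It requires event dates to be recorded, which the article does not confirm because the data items are in a supplementary file. Patients without PTA have no visit date under Table 2, so they need a status contact timed from randomization. The downside is that a fixed window may cut off some post-PTA events in late-staged patients. The descriptive summary would still show these.

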**Discussion:**

The results of the trial will, for the first time, support better decision-making for coronary evaluation before PTA in LEAD. If favorable, routine coronary angiography followed by revascularization will improve cardiovascular outcomes in LEAD patients undergoing PTA.

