We will provide a data and safety monitoring plan rather than establishing a data and safety monitoring committee because local IRBs consider that the interventions performed in the current study are medical routines. The data and safety monitoring plan includes reporting SAEs on time, increasing monitoring frequency, and analyzing safety data every 3 months. An interim analysis is performed on the primary endpoint by an independent statistician, who is blinded for the treatment allocation, when 50 % of patients have been randomly assigned and have completed 6-month follow-up. The statistician will report to the steering committee. The steering committee makes the final decision to terminate the trial and will report to the IRB of National Cheng Kung University Hospital. The trial will be ended by using symmetric stopping boundaries at a *P* value of less than 0.001. The trial will not be stopped in case of futility unless the statistician advises otherwise and the steering committee decides to terminate the trial for futility after discussion.

An adverse event that meets the criteria for an SAE between study enrollment and the end of the study will be reported to the local IRB. An SAE for this study is any untoward medical occurrence causing any of the following: a life-threatening condition, severe or permanent disability, or prolonged hospitalization. An SAE occurring after a participant withdraws consent from the study will not be reported unless the investigators consider that the event might have been caused by the protocol procedure. We will continue health care for trial participants regardless of having potential trial-related harm.

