### Statistical analysis plan

To compare baseline characteristics between routine and selective strategy groups as well as the routine strategy group and the registration group, all interval-scaled variables will be presented as mean ± standard deviation. Skewed interval-scaled data will be reported as median (interquartile range). Categorical variables will be presented as frequency and proportion (percentage). Chi-squared or Fisher’s exact test will be used for comparison of categorical variables between groups, whereas Mann-Whitney *U* test or unpaired Student’s *t* test will be used for interval-scaled variables as appropriate.

To compare the endpoints between routine and selective strategy groups, each analysis will be performed by “intention-to-treat” and “per protocol”. Proportional or Fisher’s exact test will be used for analysis of the proportion of primary, secondary, and other endpoints between routine and selective strategy groups as appropriate. For primary endpoint, significantly greater than 5 % reduction of MACE in the routine strategy group compared with the selective strategy group will be analyzed. By using the same statistical methods, subgroup analysis will include comparison of the proportion of endpoints in subgroups of these two randomized arms, such as patients with critical limb ischemia (Rutherford classification of at least 4), chronic kidney disease (at least stage 3), end-stage renal disease, old age, different genders, tobacco smoking, diabetes mellitus, hypertension, hyperlipidemia, metabolic syndrome, anemia, bedridden, hypoalbuminemia, elevated high-sensitivity C-reactive protein level, and so on. Kaplan-Meier analysis will be used to study patient survival and event-free status by using the log-rank test (Cox-Mantel) to ascertain differences between groups. If more than one endpoint occurs within the follow-up period for assessing event-free status, only the first event will be used in the analysis. Generalized estimating equation will be used to address whether and how the clustering by centers. Missing data will be treated with the multiple imputation method.

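### No named endpoint covers major bleeding, kidney injury or limb loss, so the main non-fatal harms of the two strategies have no adjudicated comparison between arms

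*Protocol article*

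**What the plan says.** All of the following is in the Protocol article.

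- **Endpoints** (Data collection and outcome measurement). The primary endpoint is long-term MACE, made up of cardiovascular death, non-fatal myocardial infarction, non-fatal stroke and unplanned coronary revascularization. For the next tier: "Pre-specified secondary endpoints include the MACE between the screening and 30 days after PTA, and the composite major coronary event on long-term follow-up". The last tier reads: "Other endpoints include death from any cause, congestive heart failure requiring hospitalization, and any coronary revascularization".
- **Adjudication** (same section). Primary, secondary and other endpoints are judged against pre-specified criteria by a committee unaware of allocation. SAEs go to the data management committee with supporting documents; no adjudication of them is stated.
- **SAEs** (Data management and monitoring). The definition covers "a life-threatening condition, severe or permanent disability, or prolonged hospitalization". SAEs are reported to the local IRB and safety data are analyzed every 3 months. There is no data and safety monitoring committee.
- **Analysis** (Statistical analysis plan). Comparisons between groups are described for baseline characteristics and endpoints. None is described for SAEs.
- **Exposure and population.** Dual antiplatelet treatment follows PCI and, on timing, "The duration from revascularization to PTA should be within 60 days" (Coronary revascularization strategy). Planned subgroups include "patients with critical limb ischemia (Rutherford classification of at least 4), chronic kidney disease (at least stage 3), end-stage renal disease" (Statistical analysis plan).
- **Purpose.** The abstract's Discussion says that the results will "support better decision-making for coronary evaluation before PTA in LEAD".

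**The concern.** The routine strategy gives every patient a coronary angiogram and, where disease is found, may lead to a stent with dual antiplatelet treatment or to bypass surgery, sometimes before PTA. Its plausible non-fatal costs are bleeding, loss of kidney function and limb loss while PTA waits. The subgroup list shows that the trial expects patients for whom these events matter most.

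The named endpoints would show a cardiac benefit with definitions, blinded adjudication and a test. The matching harms would rest on reports from sites that know the allocation. Reporting could then differ by arm for reasons unrelated to the true event rate. A MACE reduction that came with more bleeding, dialysis or amputation could be published without a dependable figure for that other side.

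**Working it through.** **1. Endpoints against harms.** There are six named endpoints:

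| Named endpoint | Major bleeding | Kidney injury | Limb loss |
|---|---|---|---|
| Long-term MACE | no | no | no |
| MACE, screening to 30 days after PTA | no | no | no |
| Long-term major coronary event | no | no | no |
| Death from any cause | if fatal | if fatal | if fatal |
| Heart failure hospitalization | no | no | no |
| Any coronary revascularization | no | no | no |

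None of the six covers a non-fatal bleeding, kidney or limb event. Stroke and peri-procedural myocardial infarction are covered through MACE.

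**2. The SAE route, step by step.**

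| Feature | Endpoints | SAEs |
|---|---|---|
| Event-specific criteria | yes | general seriousness definition only |
| Blinded adjudication | yes | not stated |
| Comparison between arms | yes | not stated |
| Regular review | interim analysis of the primary endpoint | safety analysis every 3 months |

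The SAE definition would take in a major amputation and many major bleeds or new dialysis cases. A readmission for a bleed that is neither life-threatening nor disabling may not clearly qualify, because the definition names prolonged but not new hospitalization.

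**3. Scheduled laboratory values.** Table 2 places the blood count and biochemistry at V0 only. The sample after PTA is for immunoassay, genotyping and micro-RNA (Blood sampling and measurement of biomarkers). So the schedule shown has no later creatinine or hemoglobin. Values from routine care may still exist.

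**4. The plan's own sample size.** From Power estimation and sample size calculation: 40% against 24%, superiority margin 5 points, one-sided alpha 0.05, power 80%.

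n per arm = [0.40×0.60 + 0.24×0.76] × (1.645 + 0.842)² / (0.16 − 0.05)² = 215.8, rounded up to 216; total 432. With 4% dropout, 432 / 0.96 = 450.

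The stated figures reproduce. They depend on MACE alone, so adding harm endpoints does not change them.

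**5. What harm endpoints could deliver.** The document gives no bleeding, kidney or amputation rates, so the rates below are assumptions. With n = 216 per arm:

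- 95% half-width = 1.96 × √[p₁(1−p₁)/n + p₂(1−p₂)/n]
- Power (two-sided 0.05) = Φ{(|p₁−p₂| − 1.96√[2p̄(1−p̄)/n]) / √[p₁(1−p₁)/n + p₂(1−p₂)/n]}, where p̄ is the mean of p₁ and p₂

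| Assumed rates | Difference | 95% half-width | Power |
|---|---|---|---|
| 2% vs 4% | 2 points | 3.2 points | 23% |
| 3% vs 6% | 3 points | 3.9 points | 32% |
| 5% vs 10% | 5 points | 5.0 points | 51% |
| 5% vs 12% | 7 points | 5.2 points | 74% |

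Worked line, 2% vs 4%: √[(0.0196 + 0.0384)/216] = 0.0164, and 1.96 × 0.0164 = 0.032.

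No row reaches 80% power. In the first two rows an interval centered on the assumed difference includes zero. The use of these endpoints is to bound the excess. In the first row, for example, the upper limit would be about 2 + 3.2 = 5.2 points.

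**The case against.** The strongest reply is that this is a condensed article. Its endpoint list uses the word include, it refers to Additional file 3 for the data recorded, and it has separate forms for catheterization, PCI, bypass surgery and PTA. None of these is shown. That stands: one cannot say that bleeding, creatinine or limb events go unrecorded. It does not remove the point. The article states explicitly which outcomes are named, adjudicated and compared, and these harms are not among them.

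Three stronger readings are tempting and not supported.

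- **That the trial measures no harm, so a favorable result could not inform the decision.** All-cause death, stroke and MACE from screening to 30 days after PTA capture fatal harms and the main cardiac and cerebral complications, including those while PTA is awaited. SAEs are also reviewed every 3 months. The article's own favorable conclusion is framed as cardiovascular outcomes, not net benefit over all harms.
- **That delay before PTA burdens the routine arm alone.** Patients with a positive stress test in the selective arm may be staged too, and that arm adds a test before PTA. The simultaneous approach and, at some sites, PTA first are also allowed. No figure in the document shows a longer delay in the routine arm.
- **That the excess exposure can be sized from the Background.** It gives coronary disease prevalence as up to 70% and test accuracy of around 70–75%. The first is a ceiling, and the second is not sensitivity and specificity. A count of extra angiograms or harms built on them would be assumption.

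**Conclusion.** The point holds as a gap in what will be compared, not as a failure to observe harm. None of the six named endpoints covers non-fatal major bleeding, kidney injury or limb loss. The only described route for them lacks event-specific criteria, blinded adjudication and a stated comparison between arms, and site staff are unblinded. A favorable MACE result would support the choice of strategy in part; net benefit could not be judged reliably.

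How much this matters depends on harm rates that the document does not give. Over the assumed range, harm endpoints would yield differences known to within about 3.2 to 5.2 points, which is useful for estimation and too weak for a test. The conclusion also assumes that the unseen Additional file 3 does not already define, adjudicate and compare these events. This is a cheap improvement and does not undermine the primary analysis.

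**What to change.** Add three items to the other endpoints under Data collection and outcome measurement:

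1. major bleeding, on a standard graded definition;
2. new dialysis, or sustained loss of kidney function where creatinine is already available from routine care;
3. major amputation of the index limb.

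Count them from randomization in both randomized arms, so that events before a delayed PTA are included. Collect them through the existing chart review and visits. Put them before the same blinded committee. Report each difference by randomized arm with a 95% confidence interval beside MACE, stated as estimation and not as a powered test.

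The cost is a few case report form fields, three written definitions and more events to adjudicate. No new scheduled laboratory test is needed, and the sample size stays at 450. Nothing here proposes a change to the interval around PTA or to the antiplatelet regimen.
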